#### *Symptom guided treatment (patient controlled)*

Study subjects in the first treatment arm receive treatment according to their perceived needs, i.e., they are advised to seek care when the LBP returns, gets worse, or starts to affect their functional capacity. When seeking care, they get treated according to the clinicians’ judgments. As soon as the subjects are symptom-free or satisfied with the improvement, the treatment is discontinued, but can recommence should new symptoms appear. Thus, subjects in this group are therefore treated in relation to their self-reported symptoms and this treatment arm is described as “patient controlled”.

#### *Preventive treatment (clinician controlled)*

Study subjects in the second treatment arm receive preventive treatment according to the clinicians’ judgments, i.e., they are instructed to follow a treatment plan designed to minimize the recurrence of the pain/dysfunction or to maintain the effect of the initial treatment. In this group, the clinicians’ responsibility is to be proactive and to plan a preventive treatment strategy. This group is described as the “clinician controlled” treatment arm or the MC group. Visits are scheduled at 1 to 3 month intervals according to the clinicians’ judgments. If the subjects relapse before the next scheduled visit, they are instructed to seek care and are treated according to the clinical picture until they are symptom-free or satisfied with the improvement, after which they return to the original MC plan. The total number of treatments will be the sum of scheduled and acute visits.

For all study subjects, treatment content is decided by the treating clinician and the two arms will experience the same “individualized” care with regards to modalities and recommendations. Treatment content is noted in detail in the patients’ files.

### Outcome measures

The primary outcome of the study is the number of days with bothersome pain over 12 months*.* The term bothersomeness has previously been used as a measurement for the impact of pain [29-31]. The term has been shown to correlate well with self-rated health [32], pain intensity [33], disability, psychological health (anxiety, depression), and prediction of future work absence/healthcare consultations [34], and has been suggested as a standard outcome measure in LBP research [31].

During the follow-up time of 12 months, all participants receive weekly text messages by the SMS-Track system [35,36] asking “*How many days during the previous week has your low back pain been bothersome (i.e., affected your daily activities or routines)? Please answer with a number between 0 and 7*” (requiring an answer between 0–7, sent in a reply text message). This question has not been validated against other instruments; however, it has been used in previous studies [2,27,37] in similar settings in Sweden and Denmark and has been found useful for collecting data to examine the clinical course of LBP in the primary care sector. Should the subjects fail to respond, a subsequent SMS is sent after 48 hours with a reminder. If the participants fail to respond to this second SMS, a research assistant will follow-up with a phone call to investigate the reason for non-compliance and to provide further instructions if necessary.

Secondary measures consist of self-rated health (EQ-5D [38,39], a translated (Swedish) and validated questionnaire with five domains and three answer options in each), activity limitation (the Roland Morris Disability Questionnaire, RMDQ [40], a translated (Swedish) and validated questionnaire with 24 items requiring a yes/no response), pain intensity (the Numeric Rating Scale, NRS-11 [41,42]), psychological/behavioral characteristics (the West Haven-Yale Multidimensional Pain Inventory (MPI), [43-45], a translated (Swedish) and validated 34-item, 8 scales inventory divided into two parts), self-reported work absence [46] (single question, translated (Swedish) and validated) (Table 2), and work productivity (single question, based upon the validated but not translated WPAI-instrument (LBP–V2-Swedish) [47]) (Table 2).

**Table 2 T2:** Assessment instruments and procedures

**Time**	**Instruments**	**Detailed description**
**First visit/baseline 1**	EQ-5D	Self-rated health [38]
	MPI-S	Psychological profile [43-45]
	NRS-11	Pain intensity last 24 hours [41,42]
	Descriptive data (subject)	Pregnancy (yes/no)
		Year of birth
		Pain in low back (yes/no)
		Pain in leg (yes, thigh only/yes, thigh and shin/no*)*
		Previously visited chiropractor (no/yes, more than 3 months ago/yes, less than 3 months ago*)*
		Past episodes of LBP (yes/no)
		Days in total with LBP during past year (<30/≥30)
		Pain in cervical or thoracic spine (no/yes, ≥30 days past year/yes, <30 days past year)
		Access to mobile phone (yes/no)
		Ability to send SMS text messages (yes/no)
		Belief in chance of improvement by treatment (NRS-11 varying from no chance to very probable)
		Subjective perception of health in general (5-step scale, perfect, very good, good, fair, poor)
**Baseline 2, fourth visit or earlier if indicated**	NRS-11	Pain intensity last 24 hours [41,42]
	Descriptive data (subject)	Subjective perception of health in general (5-step scale, perfect, very good, good, fair, poor)
	Descriptive data (clinician)	Clinician’s expectations concerning the response to preventive treatment
**Study start (When next visit can be scheduled at least one month ahead)**	RMDQ	Self-rated disability [40]
	Descriptive data (subject)	Sex (man/woman)
		Year of birth
		Profession (physically heavy labor/interchanging between heavy and light/ standing and walking/sitting)
	Self-reported work absence	Sick leave during past year (no/yes, 1–7 days in total/yes, 8–14 days in total/yes, ≥15 days in total)
	Descriptive data (clinician)	Type of treatment so far (manipulation, mobilization, activator, drop/soft tissue treatment/information, recommendations/other, as described by the chiropractor)
		Number of treatments during the past episode
**Random allocation**		
**Study period**	Weekly data collection for 52 weeks collected with SMS (text messages)	“How many days during the previous week has your low back pain been bothersome (i.e., affected your daily activities or routines)? Please answer with a number between 0 and 7” (requiring an answer between 0–7, sent in a reply text message [35,36])
**Follow-up after 12 months**	EQ-5D	Self-rated health [38]
	RMDQ	Self-rated disability [40]
	NRS-11	Pain intensity last 24 hours [41,42]
	Descriptive data (subject)	Other treatment in the past year? If yes, which type (physiotherapist, other chiropractor, medical doctor, medication, other)?/No
		Treatment value: considering economy, time consumption, LBP, function, quality of life, is the treatment worth continuing with? (5-step scale, definitely worth it, possibly worth it, equivocal, hardly worth it, definitely not worth it)
		Subjective perception of health in general (5-step scale, perfect, very good, good, fair, poor)
	Self-reported work absence	Sick leave during past year (no/yes, 1–7 days in total/yes, 8–14 days in total/yes, ≥15 days in total)
	Modified WPAI-LBP	Work productivity (How much has your low back pain affected your productivity during the past month, while at work? NRS-11 varying from LBP did not affect my work to LBP completely prevented me from working)
	Descriptive data (clinician)	Number of treatments including date
		Type of treatment so far (manipulation, mobilization, activator, drop/soft tissue treatment/information, recommendations/other, as described by the chiropractor)
		Reported side-effects (local soreness, fatigue, new radiating pain, other) including duration

*EQ-5D*, EuroQol 5 Dimensions; *LBP*, Non-specific low back pain; *MPI-S*, Multidimensional pain inventory, Swedish version; *NRS-11*, Numerical rating scale (11 steps, 0–10); *RMDQ*, Roland Morris Disability Questionnaire; *WPAI-GH*, Work productivity and activity impairment questionnaire – general health.

The secondary outcomes will be analyzed and reported independently of the primary outcome.

The primary utility measure of the study is quality-adjusted life years [38], and will be calculated using the EQ-5D questionnaire.

### Baseline and follow-up assessments

Baseline data at the initial visit (baseline 1) include demographic data (Table 2), pain intensity over the last 24 hours (NRS-11) [41,42], self-rated health (EQ-5D) [38], and the assessment of psychological profiles with the Multidimensional Pain Inventory, Swedish version (MPI-S) [43]. MPI-S will be used in a secondary analysis to investigate the potential interaction between the MPI subgroup and treatment effect.

During the fourth visit (or earlier if pain-free or well enough to discontinue care) (baseline 2), the subjects’ globally perceived improvement is measured using a 5-step scale (definitely worse, probably worse, unchanged, probably better, definitely better) [23] along with a follow-up NRS-11 [41,42] (for pain intensity over the past 24 hours). To assess clinicians’ expectations, the clinicians also state if they believe that their patient’s problem would benefit from preventive treatment (yes/no question).

Further baseline data are collected at the time of randomization. At that time, data regarding activity limitation (RMDQ [40]), physical work load, self-reported work absence [46], treatment content, and number of treatments are collected.

At the end of the study, both clinicians and study subjects receive a follow-up questionnaire (Table 2). The clinicians are asked to review the clinical files for treatment frequency, content, and any side-effects or adverse reactions associated with the treatment. The study subjects are asked about their pain intensity [41,42], activity limitations [40], general health [48], work absence [46] and satisfaction with care. To describe work productivity, a modified work productivity and activity impairment questionnaire, WPAI-instrument (LBP–V2-Swedish) [47] (How much has the pain affected productivity during past working month?) is used.

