### Setting

Forty Swedish chiropractors will collect data on consecutive patients with recurrent or persistent LBP. The clinicians recruited for this study have participated in a previous study regarding the use of preventive care [8] and have experience of how to integrate research into clinical practice. Only clinicians who reported that they use preventive care selectively were recruited. This was thought to minimize the clinicians’ bias towards either of the treatment models. One two-hour training session, describing the project in detail, was given to the clinicians in a small group seminar format. Following the seminar, a member of the research team has been conducting weekly follow-ups by telephone with the participating clinicians to ensure that the procedures are followed according to the project outline and that the data collection is performed correctly.

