## Discussion

Although LBP is and has been a challenge for society for many years, little is known about the preventive strategies available. Within the chiropractic profession there is a management culture with a preventive intent towards recurrent and persistent LBP. For the individual patient, the possibility of preventing episodes may be very beneficial and help keep the individual active. Furthermore, the ability to control symptoms and their effects on everyday life may be paramount. However, a preventive treatment with potential side effects and related costs can only be justified if it is demonstrated to have clinically worthwhile effects.

To date, there has been no large scale randomized clinical trial comparing chiropractic MC for LBP with symptom-guided treatment. This study will utilize available evidence in the field for the selection of study subjects, frequency of treatment, and treatment content. Furthermore, the study mimics the usual clinical procedures of chiropractic care, which will aid the transferability of the study results.

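### Side-effects come only from the treating clinician's end-of-study file review, so the opportunity to record them can differ between arms whose visits are triggered differently

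*Protocol article*

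**What the plan says.** The section on baseline and follow-up assessments describes the end-of-study data collection. For clinicians: "The clinicians are asked to review the clinical files for treatment frequency, content, and any side-effects or adverse reactions associated with the treatment". Table 2 agrees: under the 12-month follow-up, among the clinician's descriptive data, it lists "Reported side-effects (local soreness, fatigue, new radiating pain, other) including duration".

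For subjects at the same time point: "The study subjects are asked about their pain intensity [41,42], activity limitations [40], general health [48], work absence [46] and satisfaction with care". The subject rows of Table 2 add items such as other treatment received, perceived value of the treatment and work productivity, but none on side-effects.

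On visits, the preventive arm has a plan: "Visits are scheduled at 1 to 3 month intervals", with extra visits on relapse. In the symptom-guided arm nothing is scheduled. Subjects come when they perceive a need, and treatment ends once they are symptom-free or satisfied. Treatment content is said to be the same in both arms. The Blinding section states that neither subjects nor clinicians can be blinded.

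The Discussion remarks that "a preventive treatment with potential side effects and related costs can only be justified if it is demonstrated to have clinically worthwhile effects".

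**The concern.** Because content is the same in both arms, the arms differ in who triggers visits and when. A side-effect source that runs through visit files therefore depends on the feature being randomised. Soreness, fatigue or radiating pain that arises after a visit has a planned later occasion for reporting in one arm and none in the other. The person who records it knows the allocation and has already stated whether preventive treatment would benefit that patient.

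What is at stake is limited to harms. If the report sets file-based side-effects side by side by arm, the reader cannot tell how much of a difference is due to more treatment and how much to more, or better timed, occasions to mention a reaction. The Discussion names side-effects among the reasons why preventive care needs justification, so such a table is likely to be read comparatively even if it is labelled descriptive.

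**Working it through.** The plan states no side-effect rate and no recording probability, so there is no figure to reproduce. The check has two parts.

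**1. Is the file review the only route?** Each contact described in the article:

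- Weekly text message (Table 2): "How many days during the previous week has your low back pain been bothersome". No side-effect question.
- Calls to subjects (Outcome measures): after unanswered messages, "a research assistant will follow-up with a phone call to investigate the reason for non-compliance". Not described as an enquiry about harms.
- Contact with clinicians (Setting): a team member is "conducting weekly follow-ups by telephone with the participating clinicians to ensure that the procedures are followed". This concerns procedures and data collection.
- 12-month subject questionnaire: no side-effect item in the text or in Table 2.
- 12-month clinician questionnaire: side-effects taken from the files.

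Only the last collects side-effects. This is a stated method with an itemised list of instruments, not a detail left open.

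**2. What could unequal opportunity do?** Inputs from the article: 12 months of follow-up and intervals of 1, 2 or 3 months, giving 12/1 = 12, 12/2 = 6 or 12/3 = 4 scheduled visits. The symptom-guided arm has no minimum number. Assumed, not in the documents: a true reaction rate of 10% per visit in both arms, independence between visits, and recording only at a later visit.

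Share of visits followed by another visit, (k − 1)/k:

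- k = 12: 92%; k = 6: 83%; k = 4: 75%
- k = 3: 67%; k = 2: 50%; k = 1: 0%

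Patients with at least one reaction: true 1 − 0.9^k, recorded 1 − 0.9^(k − 1). For 6 preventive versus 2 symptom-guided visits:

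- True: 1 − 0.9^6 = 46.9% versus 1 − 0.9^2 = 19.0%. Difference 27.9 points, ratio 2.5.
- Recorded: 1 − 0.9^5 = 41.0% versus 1 − 0.9^1 = 10.0%. Difference 31.0 points, ratio 4.1.

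Dividing by visits does not fully repair this. Recorded reactions per visit are 0.10 × 5/6 = 0.083 versus 0.10 × 1/2 = 0.050, a ratio of 1.67 where the true ratio is 1.

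**Direction is not fixed.** Two changes to the assumptions show this:

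- Visit counts reversed: a preventive subject seen every 3 months (k = 4, 75%) against a symptom-guided subject who relapses often (k = 6, 83%) puts the better capture in the symptom-guided arm.
- Spacing: keep 6 versus 2 visits, but suppose half of the reactions are forgotten over the longer scheduled gaps and none within an episode. Recorded reactions per visit are then 0.5 × 0.083 = 0.042 versus 0.050, a ratio of 0.83. The distortion has changed sign.

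**The case against.** The strongest reply is that no planned comparison is biased. Side-effects are neither a primary nor a secondary outcome, Table 2 files them as descriptive, and the Analysis section plans no test of them. This stands, and it keeps the point modest.

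Second, no text says that a reaction enters the file only if the patient returns. It could be noted during the visit or after a telephone call, and how clinicians ask about reactions may be set out in fuller documents or in training. This also stands: recording only at a later visit is an assumption of the illustration. What remains is that the files are the only source and are built around contacts whose timing differs by arm.

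Third, a reader might infer that preventive care will look more harmful than it is. The documents do not support that. Symptom-guided visits may cluster within an episode and give prompt occasions to report, while scheduled visits 1 to 3 months apart may come after a brief reaction is forgotten. Nor do they support the idea that patients who stay away because of a reaction are lost mainly from the symptom-guided arm; no text bears on it.

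Fourth, more visits mean more true exposure, which is a real consequence of the strategy. In the first illustration, ascertainment accounts for only about 3 of the 31 points of recorded difference. This is correct on the difference scale; the ratio is affected more.

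Finally, the Discussion sentence makes worthwhile effects the test and does not promise a comparative estimate of harms. It shows why the data will interest readers, no more.

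**Conclusion.** The point holds as a limitation of the harms data. The single route for side-effects is a file review by the unblinded treating clinician, and the arms differ in what brings a patient back to that clinician. Opportunity to record can therefore differ by arm, and a descriptive between-arm statement on harms cannot separate it from true exposure.

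Size and direction are not established. The shift in ratio from 2.5 to 4.1 rests on an assumed 10% rate, assumed visit counts and an assumed recording rule, and other plausible assumptions reverse the sign. It would be wrong to conclude that the trial's safety result is biased in a known direction, or that the analysis of bothersome days is touched. An inexpensive improvement is worth making; nothing here threatens the trial's main conclusion.

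**What to change.** - Add the side-effect item already worded for clinicians in Table 2, with duration, to the 12-month subject questionnaires still to be sent. Report it by arm alongside the file-based data, as a source that does not depend on visits. It should supplement the file data rather than replace them as the main comparison.
- Report file-based side-effects per patient and per visit, using the treatment counts and dates already collected at 12 months.
- State in the report that file capture depends on attendance, so a per-visit rate does not fully correct for it.

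The cost is one item on a form that both arms already receive, by minor amendment, and one extra table; no additional visits or staff are needed. The drawbacks are 12-month recall of what may be brief reactions, by patients who know their arm, and a missing item for those who have already returned the form. Subjects randomised from April 2012 reach 12 months from April 2013, and data collection is expected to run to April 2015, so how many forms can still carry the item depends on when the change is made. If no amendment is made, the second and third steps need no new data.

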### Time line

The inclusion of study subjects started in April 2012 and is expected to proceed for a 24-month period due to the extensive inclusion protocol. The study *per se* runs over the course of 12 months and data collection is expected to be concluded during April 2015.

### Analysis

#### *Data analysis of the primary outcome “number of days with bothersome LBP”*

Intention-to-treat [49] will be used to test the null hypothesis as described in the study aim. Outcome measures will not be imputed for participants not responding to follow-up questions as previous research using the SMS-Track system has yielded high response rates [33,36,37] and research has indicated it unnecessary when performing analysis on longitudinal data [50]. Patient related outcomes measured at the fourth visit, weekly during the study period, and at the end of the study at 12 months will be evaluated using general [51] or generalized linear models [52-54] with mean baseline values as covariates. Sex, age, the presence of leg pain, patient expectations, pain intensity, the use of painkillers, sickness, albescence, type of profession, and number of treatments before being included in the study will be considered as possible confounders. All available data will be used for data analysis. A dropout analysis will be performed to compare the study population with dropouts regarding descriptive data. Additional analyses of secondary outcomes will be performed in an explorative manner.

An analysis of cost-effectiveness and cost-utility will be performed with consideration to both the individual and societal perspectives [55]. The cost-effectiveness will be determined by comparing the incremental cost effectiveness ratio in regard to the primary effectiveness measure between the two study arms [55]. Both the incremental cost effectiveness ratio and the incremental cost-utility ratio will be calculated by dividing the difference in mean total costs by the difference in the outcome of interest between the two treatment arms. Direct medical costs considered in the study are treatment cost (treatment fee) as well as time loss during treatment and travel (an average time for travel is estimated and added to an average patient visit time). Indirect costs such as production loss will be estimated using the human capital approach where lost time is valued using the hourly wage [56]. Since the data collection is performed between 2011 and 2014, all costs will be adjusted for inflation using a 3 to 5% inflation rate with the baseline year of the study as a base year [55] and calculated in €.

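### The protocol states no baseline EQ-5D adjustment for the QALY difference in the cost-utility ratio; if the QALY averages the two scheduled values, precision is lost that could be recovered at almost no cost

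*Protocol article*

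**What the plan says.** All references are to the protocol article.

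- **Ratios (Analysis, economic paragraph).** The cost-effectiveness and cost-utility ratios are "calculated by dividing the difference in mean total costs by the difference in the outcome of interest between the two treatment arms". No regression is named for either difference, and neither is called adjusted or unadjusted.
- **QALY (Outcome measures, text after Table 2).** "The primary utility measure of the study is quality-adjusted life years [38], and will be calculated using the EQ-5D questionnaire". No rule for turning EQ-5D values into a QALY is given.
- **EQ-5D schedule (Table 2; Baseline and follow-up assessments).** The initial-visit data include "self-rated health (EQ-5D". Table 2 lists EQ-5D again only at the 12-month follow-up. It is not listed at baseline 2 or at study start.
- **Baseline covariates (Analysis, first paragraph).** The models cover patient outcomes from the fourth visit, from the weekly messages and from the 12-month follow-up. Of all these outcomes the article says that they "will be evaluated using general [51] or generalized linear models [52-54] with mean baseline values as covariates". Further variables, among them what is evidently sickness absence, are only to be considered: "the use of painkillers, sickness, albescence, type of profession, and number of treatments before being included in the study will be considered as possible confounders".

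**The concern.** Cost-utility is one of the stated aims, and the QALY difference is the denominator of that ratio. The economic paragraph supplies its own formula and does not refer back to the covariate models of the paragraph before it. Those models are for outcomes measured at set times. A QALY is derived over the year, so they do not plainly cover it. An analyst following the printed text would most naturally subtract one arm mean from the other.

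With two EQ-5D values per subject, the usual area-under-the-curve QALY is their average. Half of it is then a value recorded before randomisation, which treatment cannot have affected. Any chance difference between arms in that value passes into the QALY difference and widens its standard error. The cost-utility ratio inherits that uncertainty. The value needed to remove it is already collected.

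**Working it through.** The plan gives no QALY, EQ-5D or ratio figure to reproduce, so the check concerns the form of the analysis and what it costs.

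**Inputs**

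- n = 177 per arm (Sample size).
- EQ-5D at two times, U0 (first visit) and U12 (12 months) (Table 2).
- Assumed, because the article gives none of them: QALY = (U0 + U12)/2; SDs s0 and s12, with 0.25 at both times as the main case; correlation r between U0 and U12 from 0.1 to 0.5.

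**Step 1. Formulas for the QALY difference**

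- Unadjusted variance = (2/n)(s0² + s12² + 2·r·s0·s12)/4.
- Variance after regression on arm and U0 = (2/n)·s12²·(1 - r²)/4.
- With s0 = s12 the ratio of adjusted to unadjusted variance is (1 - r²)/(2 + 2r) = (1 - r)/2. It is at most one half for any non-negative r, whatever the SD or n.

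**Step 2. Main case, SD 0.25 at both times**

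0.25 × √(2/177) = 0.0266. The unadjusted SE is this times √((1 + r)/2). The adjusted SE is this times 0.5 × √(1 - r²).

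| r | SE unadjusted | SE adjusted | Reduction |
|---|---|---|---|
| 0.1 | 0.0197 | 0.0132 | 33% |
| 0.3 | 0.0214 | 0.0127 | 41% |
| 0.5 | 0.0230 | 0.0115 | 50% |

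**Step 3. Unequal SDs**

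- s0 = 0.20, s12 = 0.25, r = 0.1: variance ratio = 0.0625 × 0.99 / (0.04 + 0.0625 + 0.01) = 0.55, so the SE falls by 26%.
- s0 = 0.30, s12 = 0.20, r = 0.5: variance ratio = 0.04 × 0.75 / (0.09 + 0.04 + 0.06) = 0.158, so the SE falls by 60%.

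These two are the ends of the range over both SD pairs and r from 0.1 to 0.5.

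**Step 4. Sensitivity to the imbalance observed**

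The baseline difference has SE 0.0266, so a 1.96-SE imbalance is 0.0521 EQ-5D units. The unadjusted QALY difference moves by (1 + r)/2 per unit of imbalance:

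- r = 0.3: 0.0521 × 0.65 = 0.034 QALY.
- r = 0.5: 0.0521 × 0.75 = 0.039 QALY.

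A simulation of 4,000 trials (200 per arm, SD 0.25, r = 0.5) agrees. The slope on baseline imbalance was 0.74 unadjusted (theory 0.75) and -0.01 adjusted. The SEs were 0.021 and 0.011. The mean error was about zero for both estimators.

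**Step 5. If the QALY uses only the 12-month value**

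The SE reduction is then 1 - √(1 - r²): 0.5% at r = 0.1 and 13% at r = 0.5.

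**Step 6. Link to the plan's own covariate model**

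Under the two-point rule, the arm coefficient from regressing (U0 + U12)/2 on arm and U0 is half the arm coefficient from regressing U12 on arm and U0, because the U0/2 part is fitted exactly. An adjusted 12-month EQ-5D analysis and an unadjusted QALY difference would therefore give different messages from the same data.

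**The case against.** The strongest reply is that the quoted sentence is only the ordinary definition of an incremental ratio. A reader might infer that the plan prescribes raw differences or rules out adjustment. The text does not support that: neither word is used, and a ratio of adjusted differences also fits the sentence. The same section plans baseline covariates for 12-month patient outcomes, EQ-5D is one of these, and both paragraphs stand under one heading. This stands, and it limits the point to what is unstated. It does not remove the point, because nothing says that those models supply the ratio's denominator.

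A reader might also infer that the cost-utility result would be biased, or that imbalance alone could decide its sign. Neither is supported. Under randomisation the unadjusted difference is unbiased, and its standard error already contains the chance imbalance. The documents give no expected QALY effect against which a change of sign could be judged. The loss is in precision.

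Third, the size rests on an unstated QALY rule and on assumed SDs and correlations. The only pre-randomisation EQ-5D precedes the initial treatment course, and the article does not say how it enters a QALY for the following 12 months. That stands, and Step 5 shows how small the gain may be.

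Fourth, this is a condensed article, and a fuller plan may name the regression. That is possible. The article nevertheless prints a formula for the ratios, and that formula can be completed in one sentence.

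**Conclusion.** The point holds as an inexpensive improvement; it does not show an error. The protocol article defines the cost-utility ratio without stating any baseline adjustment of the QALY difference, although baseline EQ-5D is collected.

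If the QALY is the two-point average and the SDs are equal, adjustment at least halves the variance for any non-negative correlation. With 177 per arm and an assumed SD of 0.25, the SE falls by about 33 to 50% for r from 0.1 to 0.5, and by 26 to 60% with the two unequal SD pairs tried. If only the 12-month value is used, the gain is 0.5 to 13%.

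A reader might extend the argument to costs, because Table 2 records "Sick leave during past year" at study start and total cost includes production loss. The documents do not support that extension. Prior absence is a four-class item, it is named only as a possible confounder and is not tied to costs, and no figure shows what adjustment would gain. The conclusion is confined to the QALY difference.

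**What to change.** Add to the economic paragraph of the Analysis section that the incremental QALY is the arm coefficient from a regression of QALY on arm and baseline EQ-5D, that this estimate is the denominator of the cost-utility ratio, and that the unadjusted difference is reported beside it. The same sentence should say how the QALY is formed from the two EQ-5D values, since the gain depends on it.

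This changes analysis wording only. It needs no new data, subjects or visits, and it should be settled before results by arm are seen. If a fuller analysis or health-economic plan already says this, a cross-reference is enough.

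### Travel is costed as time only, so the incremental cost is misstated, in favour of whichever arm makes more visits, by the visit difference times the expense per trip

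*Protocol article*

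**What the plan says.** All of the economic plan is in the second paragraph of the Analysis section of the protocol article.

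- **Perspective.** "An analysis of cost-effectiveness and cost-utility will be performed with consideration to both the individual and societal perspectives".
- **Direct costs.** "Direct medical costs considered in the study are treatment cost (treatment fee) as well as time loss during treatment and travel". In full, the second item reads "time loss during treatment and travel (an average time for travel is estimated and added to an average patient visit time"; the parenthesis says how the time is obtained.
- **Indirect costs.** "Indirect costs such as production loss will be estimated using the human capital approach where lost time is valued using the hourly wage".
- **Ratios.** Both the cost-effectiveness and the cost-utility ratio are formed by "dividing the difference in mean total costs by the difference in the outcome of interest between the two treatment arms".

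On visits, the section on the preventive arm spaces scheduled visits 1 to 3 months apart, allows extra visits on relapse, and states: "The total number of treatments will be the sum of scheduled and acute visits". The section on the symptom-guided arm has patients attend when they feel the need and gives no number. Table 2 has the clinician report the number and dates of treatments at 12 months. It has no item for distance, mode of transport or trip expense.

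**The concern.** Someone who travels to a clinic gives up time and usually also spends money. The plan prices the first and does not name the second. Under the two perspectives chosen, both are costs of a visit: the patient pays the fare or fuel, and society bears the resource use.

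The abstract and the Analysis section recognise only direct medical costs and indirect costs. Trip expense is not in the direct list, and it does not fit the indirect item, which values lost time at a wage. An analyst who followed the text would leave it out.

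The omission grows with the number of visits, and the visit pattern is what the two arms are designed to differ in. It therefore cancels in the cost difference only if both arms make the same mean number of visits. Cost-effectiveness and cost-utility are stated in the study aim, so the cost difference is a reported result of the trial.

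**Working it through.** The plan states no cost figure, so there is none to reproduce. The check is an identity followed by assumed ranges.

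**Inputs from the protocol article**
- Follow-up: 12 months (Procedures).
- Preventive visits: one every 1 to 3 months, plus acute visits (Preventive treatment).
- Symptom-guided visits: on perceived need, no number (Symptom guided treatment).
- Cost per visit: fee *F* plus value of visit and travel time *T* (Analysis).

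**Inputs that are assumptions**
- Expense per return trip, *c*: EUR 3 to 15, taken as equal in both arms.
- Difference in mean visits, preventive minus symptom-guided, *D*: -2 to +6.

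**Step 1: scheduled visits in the preventive arm.** 12 / 3 = 4 and 12 / 1 = 12, so about 4 to 12 a year before acute visits. This describes one arm; it is not the difference between arms.

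**Step 2: cost per visit.** Planned: *F* + *T*. With the trip expense: *F* + *T* + *c*. An arm with mean visits *V* is understated by *V* x *c*.

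**Step 3: incremental cost.** Cost difference with the trip expense minus cost difference as planned = *D* x *c*. Positive values mean that the plan understates the incremental cost of the preventive arm.

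| *D* (visits) | *c* = EUR 3 | *c* = EUR 8 | *c* = EUR 15 |
|---|---|---|---|
| -2 | -6 | -16 | -30 |
| 0 | 0 | 0 | 0 |
| +2 | 6 | 16 | 30 |
| +4 | 12 | 32 | 60 |
| +6 | 18 | 48 | 90 |

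The range is EUR -30 to +90 per patient-year.

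**Step 4: share of the visit cost.** With an assumed fee of EUR 25 to 50 and an assumed time value of EUR 15 to 30, the omitted share *c* / (*F* + *T* + *c*) runs from 3 / (50 + 30 + 3) = 3.6% to 15 / (25 + 15 + 15) = 27.3%.

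**Step 5: ratios.** The ratio shifts by *D* x *c* / *E*, where *E* is the benefit difference (pain days avoided or QALYs gained, preventive minus symptom-guided). For *D* x *c* = EUR 32 and an assumed *E* of 0.01 to 0.02 QALYs, the shift is 32 / 0.02 = EUR 1,600 to 32 / 0.01 = EUR 3,200 per QALY. For *E* = -0.01 it is EUR -3,200 per QALY, in the opposite direction. For *E* near zero the ratio is unstable with or without the trip expense.

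**The case against.** The strongest reply is that an article compresses the economic plan into one paragraph and that itemised unit costs belong in a fuller document. A fare is ordinarily classed as a direct non-medical cost, so a sentence about direct medical costs need not mention it. The parenthesis explains how time is estimated and does not say that expense is excluded. This has some force: the text contains no explicit exclusion. But the sentence reads as the list of what is considered, it already places patient time under the medical heading, and it specifies how travel enters. The point rests on that stated costing rule and not on silence alone.

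The second reply concerns direction, and it stands. A reader might infer that the preventive arm is bound to look cheaper than it is. The documents do not support that. The 4 to 12 visits are that arm's schedule. Symptom-guided patients who relapse are treated until symptom-free or satisfied, which can take several visits per episode, and preventing such episodes is the purpose of the other arm. The difference could be zero or negative.

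The third reply also stands. A reader might infer that both ratios are biased towards the preventive arm. That requires more visits and a better outcome in that arm, neither of which is known. Other items outside the direct-cost list, such as the other treatment and medication recorded in Table 2, could also differ between arms, so a net bias cannot be read from this one item.

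**Conclusion.** The point holds as a gap in the stated costing rule. As written, the plan leaves the expense of each trip out of analyses promised "with consideration to both the individual and societal perspectives", and the incremental cost is misstated by the visit difference times the expense per trip, to the advantage of the arm that attends more. The preventive arm is the likelier one, because it alone has scheduled visits, but the documents do not settle this. The error vanishes with equal mean visits and reverses if the symptom-guided arm attends more.

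The size, EUR -30 to +90 per patient-year, rests wholly on the assumed ranges. No total cost, outcome difference or decision threshold is given, so nothing shows that a conclusion would change. The matter is minor: it concerns one component of the economic analysis and leaves the primary outcome and the sample size untouched.

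**What to change.** In the economic paragraph of the Analysis section, add an average travel expense per visit to the unit cost of every visit, in both arms and both perspectives. State it as an average distance multiplied by a mileage or fare rate, and give the source of each. Apply it to the visit counts that clinicians already report at 12 months.

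Add a one-way sensitivity analysis that varies this expense over a stated range including zero, so that readers can see whether the ratios depend on it. The section describes no sensitivity analysis at present, so this would be new. If the expense is left out on purpose, the section should say so and give the reason.

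The cost is small. No further patient data are needed, but Table 2 records neither distance nor mode of transport, so the unit cost will be an assumption. The arm with more visits may look slightly less favourable.
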